### Ethical considerations

This study was approved by the Research Ethics Committee of the UNIFESP under approval number 48165521.3.0000.5505, by the Research Ethics Committee of the *Hospital e Maternidade* SEPACO, by the Research Ethics Committee of the *Hospital São José*, and by the Research Ethics Committee of the *Hospital das Clínicas* of the *Faculdade de Medicina* of the USP. All participants or their legally authorized representatives will provide signed informed consent.

Participant inclusion will begin only after formal ethical approval. Investigators are committed to following international Good Clinical Practice requirements and the Declaration of Helsinki, and to adhering to national ethical standards set forth in the National Health Council Resolutions 466/2012 and 510/2016, ensuring the ethical conduct of the study and the safety of participants.

Only initials and hospital registration numbers will be recorded. All clinical and study-related information will be treated confidentially. Clinical records will be stored in areas with restricted access, limited to investigators and delegated data collection staff.

### Statistics

#### Sample size calculation and interim analysis

Based on a pilot study (data not shown), we expected the primary outcome to occur in 90% of the participants in the usual care group. Based on a previously published outpatient's clinic study, we expected an absolute reduction of 15% among those participants receiving methylene blue. Considering a 90% power and assuming a two-tailed alpha of 0.05, 130 participants would be required in each group.

An interim analysis will be performed after the inclusion of 100 participants to assess potential safety issues with the intervention regarding the primary outcome. The DSMB will review adverse event, compliance, and safety data. We do not plan to stop the study for futility or superiority. We plan to stop the study for safety using a stopping rule with a p-value < 0.01 for harm at the interim analysis. The DSMB will provide a recommendation based on the data, external evidence, and safety profile.

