**Methods::**

BLUE is a randomized, multicenter, open-label trial. Patients with high risk of hypotension during renal replacement therapy will be randomized to receive either methylene blue infusion at a dose of 1mg/kg as a bolus, followed by continuous infusion of 0.1mg/kg of body weight in a total of 200mL of saline solution throughout the dialysis session, or to usual care. The usual care group will not receive any intervention. A total of 260 patients is expected to be randomized in a 1:1 ratio.

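### The formal interim harm rule (p < 0.01, about 50 per arm) is tied to an outcome expected in 90% of controls, so it has very little power to detect harm

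*Protocol article*

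**What the plan says.** All of the rule stands in the Protocol article, under Sample size calculation and interim analysis.

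- Timing and endpoint of the look: "An interim analysis will be performed after the inclusion of 100 participants to assess potential safety issues with the intervention regarding the primary outcome".
- Boundary: "We plan to stop the study for safety using a stopping rule with a p-value < 0.01 for harm at the interim analysis". Stopping for futility or superiority is ruled out in the same paragraph, so this is the only formal boundary in the trial.
- Expected control rate: "we expected the primary outcome to occur in 90% of the participants in the usual care group".
- Other material for the board: "The DSMB will review adverse event, compliance, and safety data". Its recommendation may also draw on external evidence and the safety profile. No numerical criterion is attached to any of this.

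The sentence with the boundary names no endpoint, no test and no sidedness. The endpoint has to be taken from the sentence that sets up the interim look.

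**The concern.** A harm boundary needs an outcome that has room to get worse. An outcome expected in 90% of controls has only 10 points of room, and 50 patients per arm cannot reliably separate 90% from 95% or even from 100% at p < 0.01. Death, myocardial infarction and cardiopulmonary arrest are collected but carry no boundary.

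What is at stake is how a boundary that is not crossed would be read. The Introduction says that, to the authors' knowledge, methylene blue has not been used in a randomized study during RRT in critically ill patients. In that setting a result that is close to uninformative could be taken as reassurance.

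**Working it through.** **Inputs.** From the sample size section: control rate 0.90, planned reduction 0.15, power 90%, two-sided alpha 0.05, 130 per group, interim at 100 participants, harm threshold p < 0.01. From the abstract: 1:1 allocation, hence about 50 per arm at the interim. Assumptions: exactly 50 per arm and an unadjusted comparison.

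**The plan's own figure.** With unpooled variance, n = (1.960 + 1.282)² × (0.90 × 0.10 + 0.75 × 0.25) / 0.15² = 10.51 × 0.2775 / 0.0225 = 129.6, so 130 per group. The stated sample size is reproduced, which confirms the 90% control rate as the design value.

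**Worst case at the expected counts: 50/50 versus 45/50.**

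- Pearson: z = 0.10 / √(0.95 × 0.05 × 2/50) = 0.10 / 0.0436 = 2.29; two-sided p = 0.022, one-sided p = 0.011.
- Fisher, two-sided: 2 × C(50,5) / C(100,5) = 2 × 2,118,760 / 75,287,520 = 0.056.
- Other two-sided tests: Yates 0.067, Barnard 0.024, Boschloo 0.035, unpooled Wald 0.018.
- Tests that do reach 0.01: likelihood ratio (0.007) and one-sided unpooled Wald (0.009).

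**How low controls must fall when methylene blue is at 50/50.** To reach p < 0.01, the control count must be at most 42 by two-sided Fisher (43/50 gives 0.012, 42/50 gives 0.006), 43 by two-sided Pearson (44/50 gives 0.012, 43/50 gives 0.006), 44 by one-sided Pearson, or 45 by likelihood ratio.

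**Chance that the rule fires.** The two binomials with n = 50 are enumerated exactly, counting tables with p < 0.01 in the direction of harm. When the true methylene blue rate is 100%, this is simply P(X ≤ cut-off) for X ~ Bin(50, 0.90).

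| Test | 100% vs 90% | 95% vs 90% |
|---|---|---|
| Fisher, two-sided | 12% (X ≤ 42) | 1.5% |
| Pearson, two-sided | 23% (X ≤ 43) | 3% |
| Pearson, one-sided | 38% (X ≤ 44) | 6% |
| Likelihood ratio | 57% (X ≤ 45) | 7% |

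Halving the likelihood-ratio p-value, the most liberal choice tried, gives 75% and 11%.

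**If the interim uses the analysis set of the Statistical analysis section**, patients who never receive RRT drop out. With 45 per arm (assumed), the 100% versus 90% figures fall to about 16% (Pearson) and 8% (Fisher).

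**The same p < 0.01 rule on other outcomes, 50 per arm.** The documents give no rates for these, so all are assumed.

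| Control vs methylene blue | Pearson | Fisher |
|---|---|---|
| 5% vs 10% | 3.2% | 1.5% |
| 5% vs 15% | 16% | 10% |
| 5% vs 25% | 62% | 53% |
| 40% vs 50% | 6% | 4% |
| 40% vs 65% | 50% | 42% |

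At gaps of 5 to 10 points these outcomes do no better than the primary outcome. Their advantage is that larger gaps are possible at all.

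**The case against.** A reader might infer that the rule can never fire at the planned control rate. The documents do not support that. The 90% is an expectation, and the observed control count can fall to 42 or 43 of 50 by chance. The interim test is also unnamed, and a likelihood-ratio test would cross even at 45/50.

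A reader might also infer that the trial has no working safety oversight. That fails too. The board sees adverse event and safety data and is not bound to the p-value, and the Safety and adverse events section adds independent adjudication of serious adverse events and reporting to the board. A board charter, not shown, may say more.

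Nor is it fair to say that the composite is no measure of harm: more vasopressor escalation or more interrupted sessions on the drug would be haemodynamic worsening. Its defect is the ceiling.

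Finally, the boundary sentence does not itself name the primary outcome. Linking the two is an inference, but the natural one, since the look is set up "to assess potential safety issues with the intervention regarding the primary outcome".

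These points limit the finding to the formal boundary. They do not remove it. No numerical criterion covers death or serious events. The adverse event definition also sets aside events judged expected or due to the underlying illness, which can thin the comparison between arms on which the board's discretion would rest.

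**Conclusion.** The point holds as a matter of low sensitivity. On an outcome expected in 90% of controls, the only formal harm boundary can see an excess of at most 10 points. By the usual two-sided tests it fires in about 12% to 23% of trials in the most extreme case possible, and in 1.5% to 3% at a 5-point excess. One-sided Pearson or the likelihood-ratio test raises this only to 38% to 57% and 6% to 7%.

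This rests on 50 per arm, an unadjusted comparison, a true control rate of 90%, and reading the boundary as applying to the primary outcome. If the true control rate were lower there would be more room: at 80% versus 95%, for example, the rule fires in 38% (Pearson) or 28% (Fisher) of trials. The final efficacy inference is not affected, and the weakness should not be described as an absence of safety monitoring.

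**What to change.** In the interim analysis paragraph, and in the DSMB charter:

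1. Apply the p < 0.01 harm boundary to outcomes already collected that have room to show harm: all-cause death within a fixed window that is known at the interim (for example, within 24 hours or at the data cut), and the serious events listed under Outcomes (acute myocardial infarction, cardiopulmonary arrest).
2. Count these by arm in all randomized participants, regardless of attribution.
3. Name the test and its sidedness.
4. Give the board the primary outcome by arm as supporting data.
5. State that at about 50 per arm the boundary detects only large excesses, so failure to cross it is not evidence of safety.

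The cost is one paragraph in each document. No efficacy alpha is spent, because no superiority stop is planned. With a two-sided p < 0.01 counted only in the harmful direction, the chance of a false harm signal is up to about 0.5% per outcome. It is lower for rare events: about 0.1% by Pearson if both arms have a 5% rate (assumed).

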#### Statistical analysis

Our primary analysis will follow a modified intention-to-treat (mITT) approach, including all randomized participants who consent to participate. As clinical management might change after randomization, we expect that some participants randomized will not undergo RRT, either because of clinical improvement or deterioration. Thus, mITT analysis will include only those participants who received RRT. The data analysis will be performed after the submission of the protocol paper and analysis plan for publication.

Categorical variables will be expressed as counts and percentages. Continuous variables will be presented as means and standard deviations (SD) or medians with interquartile ranges (IQR, 25^th^ - 75th percentile), as appropriate. For all outcomes, including the primary outcome, we will not impute missing data, and the number of missing values will be clearly presented in tables. Treatment adherence will be reported as receiving the medication as a bolus, as a continuous infusion, or both.

The composite primary outcome will be measured using a mixed logistic model adjusted for non-linear terms of age, baseline MAP, vasopressor dose, and study site. Vasopressor dose will be defined as noradrenaline dose equivalents.^(15)^ A per-protocol analysis will be performed, including only participants who received the assigned medication. Additionally, we will conduct a sensitivity analysis that considers only participants who received the medication as a bolus plus continuous infusion. In all primary outcome analyses, the estimand will be the marginal risk difference between the intervention and control groups, along with their 95% confidence intervals, using the R package. Odds ratios will also be reported. Age and MAP will be included as restricted cubic splines in the model. In case any model does not converge, a stepwise approach will be used: (1) remove cubic splines; (2) remove the random effect for the site; (3) use Poisson or binomial regression.

Secondary outcomes will be assessed using similar models for categorical outcomes and using linear models for continuous variables, with adjustment for age, baseline MAP, vasopressor dose. For secondary binary and exploratory outcomes, logistic regression will be used, with the effect estimate expressed as marginal differences. The frequency of adverse events will be expressed as counts and percentages, and comparisons.

To demonstrate changes in physiological variables over time, we will present box plots. We will compare differences between groups in a mixed model, adjusting for age and baseline NEE, including participants as random effects, time and treatment as fixed effects, and treatment-by-time interactions.

For the primary outcome, we will perform a sensitivity analysis on the use or non-use of vasopressors at the initiation of dialysis therapy and at the first dialysis session *versus* non-use. We hypothesize that methylene blue will have more pronounced effects in patients without vasopressors and patients on their first dialysis session.

We will consider a significant two-tailed p level ≤ 0.05. Analysis will be performed using the current version of R (R Foundation for Statistical Computing, Vienna, Austria).

We do not expect participants to have missing outcome data for the primary composite outcome and the secondary outcome. If, for some reason, missing data occur because the researchers have not entered the data, we plan to perform multiple imputation. If a patient dies within the 24 hours time frame of the secondary outcomes, we will not make data imputations. For the physiological variables that will be compared over time, we will not make imputations, as the mixed model handles missing data as missing at random. If a patient dies within the 24 hours time frame of this data collection, we will use the last observation carried forward (as the most likely worst value of the physiological variable) to present these physiological analyses.

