### Randomization and allocation concealment

Participants will be randomized to receive either methylene blue or usual care through a centralized, web-based automated randomization system (RedCap® UNIFESP). The randomization list will be generated electronically on random.org by an external individual not involved in the study, using variable block sizes of 4 - 6, stratified by center and prior vasopressor use. Randomization access will be available 24 hours a day, 7 days a week. Each registration number will be randomized only once to prevent the same participant from being randomized more than once in the study. Randomization will be carried out automatically without the investigators’ knowledge. The participating centers were unaware of the block sizes to ensure allocation concealment. The flowchart is available in figure 1.

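### The listed models carry the randomisation strata only in part, the fallback drops site without a fixed-effect replacement, and its last step leaves the error model open

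*Protocol article*

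**What the plan says.** **Randomisation.** Under Randomization and allocation concealment, the list is "stratified by center and prior vasopressor use".

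**Primary model.** The Statistical analysis section gives a mixed logistic model with age, baseline mean arterial pressure (MAP), vasopressor dose in noradrenaline equivalents, and study site. The fallback shows that site is a random effect. The effect measure is the marginal risk difference.

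**Secondary models.** Categorical outcomes get models similar to the primary one. Continuous outcomes are analysed "using linear models for continuous variables, with adjustment for age, baseline MAP, vasopressor dose"; site is not in that list.

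**Longitudinal model.** Physiological variables over time are compared in a mixed model "adjusting for age and baseline NEE, including participants as random effects", with time, treatment and their interaction. Neither site, nor vasopressor use as yes/no, nor the baseline of the variable analysed is listed.

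**Fallback.** If any model does not converge, the order is "1) remove cubic splines; (2) remove the random effect for the site; (3) use Poisson or binomial regression".

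**The concern.** Randomising within strata pays off fully when the analysis conditions on the same strata. Three mismatches stand out.

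- The vasopressor stratum is yes/no, but the models hold only a dose. A dose term separates users from non-users, yet it need not capture a step in risk at zero. Such a step is plausible. Under Eligibility criteria, non-users qualify only through low systolic pressure. Under Outcomes, the vasopressor component of the composite is starting the drug for non-users and a rise of at least 20% for users.
- When the mixed model fails, site leaves the model. With five ICUs, a fixed effect is the natural replacement, and none is named.
- Step 3 offers two model families with no rule for choosing between them. One of them, with its default standard errors, is badly calibrated for a binary outcome as common as this one. The choice would fall after the planned model had failed on the trial data.

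At stake are a little precision in the usual case and, in one remote branch, most of the trial's power.

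**Working it through.** **Inputs** (Sample size calculation and interim analysis): "we expected the primary outcome to occur in 90% of the participants in the usual care group"; "we expected an absolute reduction of 15% among those participants receiving methylene blue", so 75%; "Considering a 90% power and assuming a two-tailed alpha of 0.05"; "130 participants would be required in each group".

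**1. The plan's own figure.** Unpooled normal approximation:

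n = (0.90×0.10 + 0.75×0.25) × (1.960 + 1.282)² / 0.15² = 0.2775 × 10.51 / 0.0225 ≈ 129.6, so 130 per group. The stated size reproduces.

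**2. Standard error of the risk difference, 130 per arm.**

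- Binomial variance p(1−p): √[(0.09 + 0.1875)/130] = 0.0462.
- Poisson model-based variance p: √[(0.90 + 0.75)/130] = 0.1127.
- Ratio: 0.1127 / 0.0462 = 2.44.

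**3. The same on the log risk ratio.**

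- Binomial: √[0.10/(130×0.90) + 0.25/(130×0.75)] = 0.0585.
- Poisson model-based: √[1/(130×0.90) + 1/(130×0.75)] = 0.137.
- Ratio: 2.35.

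If both arms had the same rate, the ratio would be 2.0 at 75% and 3.16 at 90%.

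**4. Effect on one data set.** Take 117/130 against 98/130, a risk difference of −14.6 points. The 95% interval is −36.7 to +7.5 with model-based Poisson errors and −23.6 to −5.6 with robust errors.

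**5. Power in that branch.** Significance with model-based errors needs an observed difference above 1.96 × 0.1127 = 0.221. The estimate actually varies with standard error 0.0462 around 0.15. Power is therefore about 1 − Φ[(0.221 − 0.15)/0.0462] = 1 − Φ(1.53) ≈ 6%. Summing exactly over all two-arm binomial outcomes gives 6.9% on the risk difference and 6.7% on the log risk ratio, against 90–91% with the correct variance. The shortcut Φ(0.15/0.1127 − 1.96) gives 26%. It is wrong here because it treats the test statistic as having unit variance, when its standard deviation is about 0.0462/0.1127 = 0.41.

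**6. Direction.** The error is conservative. In 1,500 simulated trials with no effect and assumed stratum effects, model-based Poisson rejected in 0%.

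**7. Cost of omitting the strata alone.** With site risks assumed to run from 70% to 98%, the unadjusted standard error was about 2% too large and the type I error 4.4%. In the simulation of step 6, logistic regression rejected in 4.1% of trials without the strata and 5.7% with them. The Monte Carlo standard error is √(0.05×0.95/1500) = 0.6 points, so both are compatible with 5%.

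**The case against.** **The strata are not ignored.** A reader might infer that the models leave out the randomisation factors. The primary model does not: it has site, and a dose that is zero for non-users carries much of the second stratum. The plan also examines the primary outcome by vasopressor use. What is missing is an explicit yes/no adjustment term. Nor is the dose term clearly a straight line: one sentence speaks of non-linear terms before listing dose, while a later one names splines only for age and MAP.

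**The 2.4-fold inflation needs three things at once:** step 3 is reached, Poisson is chosen over binomial, and model-based variance is used. By step 3 the splines and the random effect are gone, leaving a logistic model with treatment and three covariates and about 13 + 32.5 = 45.5 expected non-events. In 3,000 simulated trials at the planned rates, with assumed covariate and site effects, that model never failed or separated. The article names no variance estimator, and an article may leave that to the full analysis plan. It would therefore be wrong to say that the plan uses plain Poisson errors, or that a true benefit would be reported as non-significant.

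**Two further inferences fail.** That a failed fit is likely with five sites is not shown; a site variance estimated at zero is a boundary estimate, not necessarily non-convergence. That binomial regression adds nothing after a failed logistic model is also wrong: with an identity link it estimates a risk difference directly.

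**The gaps in the other models are partly open to reading.** Similar models for categorical outcomes may include site. If baseline is one of the longitudinal time points, the treatment-by-time term already compares change from baseline.

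All of this stands. It leaves untouched that step 2 removes site with nothing in its place, that the yes/no stratum is absent, that site is not listed for the continuous secondary and longitudinal models, and that step 3 is an open fork.

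**Conclusion.** The point holds as a matter of specification with a small expected effect. The strata used to randomise are only partly in the listed models, and the fallback discards one of them where a fixed effect would serve. The likely loss is slight and conservative, about 2% on the standard error under the assumed spread of site risks.

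The large figures (a standard error about 2.4 times too large on the risk difference, power about 7% against about 90%) describe a worst case. They rest on the planned 90% and 75%, 130 per arm, no covariates, and the three conditions above. They show why step 3 should be pinned down; they do not forecast what the trial will report. Nothing here inflates the type I error or puts the sample size in doubt.

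**What to change.** - **Primary, secondary and longitudinal models:** include site, and add prior vasopressor use (yes/no) alongside dose.
- **Longitudinal model:** add the baseline value of the variable analysed, unless baseline is already one of its time points.
- **Fallback step 2:** replace the site random effect with a fixed site effect (five ICUs, 4 df).
- **Fallback step 3:** keep both strata, state how the choice between Poisson and binomial is made, and require robust (sandwich) variance if Poisson is used.
- **Effect measure:** obtain the marginal risk difference by standardisation at every step.

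The cost is about 5 degrees of freedom in 260 participants (4 for site, 1 for vasopressor use) and a change of wording, to be fixed before the data are analysed. It needs no new data and no more participants.

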### Outcomes

The primary outcome will be a composite consisting of any of the following events: (1) initiation of vasopressor therapy or an increase in vasopressor dose by at least 20% from baseline; (2) interruption of the RRT session; (3) interruption of fluid removal at the request of the attending physician at any point during the session. No predefined interruption criteria were established due to the wide range of clinical scenarios encountered in patients undergoing RRT; thus, decisions regarding treatment interruption were left entirely to the attending physician's discretion and will not be adjudicated.

Secondary outcomes include the occurrence of hypotension during the RRT session, the maximum vasopressor dose within the first 24 hours after the hemodialysis session, the cumulative norepinephrine equivalent (NEE) dose,^(15)^ the RRT session fluid balance, the 24-hour fluid balance, ICU mortality, and in-hospital mortality. Hypotension will be defined as a sustained drop in mean arterial pressure (MAP) below 65mmHg. We will assess potential adverse events related to methylene blue use, specifically: acute myocardial infarction, hemolytic anemia, cardiopulmonary arrest during the session, and worsening of gas exchange. We will present all outcome data as specified in table 1S (Supplementary Material). The trial sequence is available in figure 2.

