### Data collection

Demographic characteristics, comorbidities, and severity of illness will be collected at baseline for all participants (Table 2S - Supplementary Material). Renal replacement therapy main characteristics and baseline hemodynamic data will be collected (Table 3S - Supplementary Material), and vital signs will be recorded every 15 minutes by the nursing team via invasive blood pressure or automated non-invasive blood pressure for the duration of the session, along with any changes in vasoactive drug use (Table 4S - Supplementary Material). We will collect variables assessed up to 24 hours, then participants will be followed until hospital discharge to determine survival status or death.

Participants who are withdrawn from the study for safety reasons (excluding those who withdraw consent) will be included in the analysis on an intention-to-treat basis. Any adverse events occurring within the first 24 hours after the hemodialysis session will be documented (Table 5S - Supplementary Material). Adherence to the intervention will also be recorded (Table 6S - Supplementary Material). The data collection schedule is presented in table 7S (Supplementary Material).

Data will be collected via electronic forms using the RedCap platform and securely stored. Forms will be completed by the investigators, who will use specific passwords to access them. Training will be provided for all personnel involved in the study to ensure high-quality data collection. The principal investigator will be available for any questions regarding form completion. Data consistency will be periodically reviewed, and any discrepancies will be addressed by contacting the sites for clarification and correction.

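### The ICU and in-hospital mortality models leave out the baseline severity of illness that the trial collects, at a modest cost in precision

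*Protocol article*

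**What the plan says.** All references are to the protocol article.

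- **Primary model** (Statistical analysis): a "mixed logistic model adjusted for non-linear terms of age, baseline MAP, vasopressor dose, and study site".
- **Secondary outcomes** (Statistical analysis): "Secondary outcomes will be assessed using similar models for categorical outcomes", with linear models for continuous outcomes, "with adjustment for age, baseline MAP, vasopressor dose". For secondary binary outcomes, "logistic regression will be used, with the effect estimate expressed as marginal differences".
- **Mortality is among them** (Outcomes): the list of secondary outcomes ends with "the 24-hour fluid balance, ICU mortality, and in-hospital mortality".
- **Severity is collected** (Data collection): "Demographic characteristics, comorbidities, and severity of illness will be collected at baseline for all participants". The instrument, its timing and its components are not in the text available; they may be in supplementary Table 2S, which is not shown.

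Severity of illness is named in none of the models in the Statistical analysis section, and no reason for leaving it out is given. Randomisation is stratified by centre and prior vasopressor use, so the design does not balance overall severity directly.

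**The concern.** The same three covariates serve a pressure outcome during one dialysis session, fluid balance, vasopressor dose and death. For death in critically ill patients, a general measure of severity would usually be expected to predict outcome beyond age, blood pressure and vasopressor dose. Where a baseline variable predicts the outcome, adjusting for it narrows the interval and removes from the estimate the part of any chance imbalance that it explains.

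Precision on mortality matters here for two reasons. Adverse events are collected for 24 hours only, and participants are then followed only for survival to hospital discharge, so mortality is the only planned information on harm beyond the first day. The trial is also open-label, and its primary composite rests largely on treatment decisions that are not adjudicated, so readers will look to mortality as a check.

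Timing matters too. A severity covariate named before analysis is unremarkable; one added after an imbalance has been seen looks chosen for its effect on the result.

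**Working it through.** **1. The plan's own figure.** The sample size rests on the primary outcome: "we expected the primary outcome to occur in 90% of the participants in the usual care group" and "we expected an absolute reduction of 15% among those participants receiving methylene blue", that is 90% against 75%, with 90% power and two-sided alpha 0.05. With unpooled variance,

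n per group = (1.960 + 1.282)² × (0.90 × 0.10 + 0.75 × 0.25) / 0.15² = 129.6, so 130.

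The stated 130 per group reproduces (the pooled formula gives 133; power at 130 is 0.894). Nothing in it was sized for mortality.

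**2. What 130 per group gives for mortality.** No expected mortality is stated, so 30% to 60% is assumed. The unadjusted half-width is 1.96 × √(2p(1 − p)/130):

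| Assumed mortality | Half-width (points) | Power for a 10-point reduction |
|---|---|---|
| 30% | 11.1 | 46% |
| 40% | 11.9 | 39% |
| 50% | 12.2 | 37% |
| 60% | 11.9 | 37% |

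**3. What adding severity gains.** Simulation of 4,000 trials of 260 patients per scenario, 130 per arm. The analysis is logistic regression standardised to a marginal risk difference, first with three covariates and then with severity added. All of the following are assumptions:

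- mortality about 48%;
- standardised age, MAP and vasopressor dose with log-odds 0.35, −0.15 and 0.45 per SD;
- treatment log-odds −0.4;
- severity log-odds 0.3 to 1.1 per SD;
- severity correlated 0 or 0.5 with the prognostic combination of the three listed covariates;
- no site effect.

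Gain in effective sample size = (SE with three covariates / SE with four)² − 1, computed from unrounded standard errors. Half-width reduction = 1.96 × (difference in SE).

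| Severity log-odds per SD | Correlation | SE, three covariates | SE, with severity | Gain in effective sample size | Half-width reduction (points) |
|---|---|---|---|---|---|
| 0.3 | 0 | 0.0602 | 0.0596 | 2.1% | 0.1 |
| 0.3 | 0.5 | 0.0603 | 0.0600 | 0.9% | 0.1 |
| 0.5 | 0 | 0.0600 | 0.0582 | 6.3% | 0.4 |
| 0.5 | 0.5 | 0.0581 | 0.0570 | 4.0% | 0.2 |
| 0.8 | 0 | 0.0596 | 0.0562 | 12.5% | 0.7 |
| 0.8 | 0.5 | 0.0579 | 0.0552 | 9.9% | 0.5 |
| 1.1 | 0 | 0.0613 | 0.0552 | 23.5% | 1.2 |
| 1.1 | 0.5 | 0.0564 | 0.0528 | 14.4% | 0.7 |

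A separate simulation (800 replicates, mortality about 50%, severity correlated with age and vasopressor dose) gave standard errors of 0.0594 against 0.0582, 0.0587 against 0.0559 and 0.0581 against 0.0535. The squared ratios are 1.04, 1.10 and 1.18, inside the same range.

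**4. Bias.** In every scenario of step 3 the mean risk difference was the same to three decimals with and without severity.

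**5. Chance imbalance.** The standard error of the between-arm difference in a standardised score is √(2/130) = 0.124 SD. At 50% mortality and 0.8 log-odds per SD, an imbalance of one standard error moves the mortality difference by up to 0.25 × 0.8 × 0.124 = 0.025, about 2.5 points, less what the listed covariates absorb. This is random error that the interval already covers.

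**6. Why the primary model is left alone.** Expected participants without the primary event: 260 × 0.10 = 26 if there is no effect, and 130 × 0.10 + 130 × 0.25 = 45.5 as planned. Age and MAP already enter that model as splines, so there is little room for more terms.

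**The case against.** The strongest reply is that nothing here is wrong. Three prognostic baseline covariates are pre-specified, the effect measure is marginal, and randomisation makes the contrast valid. MAP and vasopressor dose already carry part of acute severity, and a site term may carry over from the primary model, so the set may be wider than three. That stands: this is a point about efficiency, and the text does not contradict itself.

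A second reply is that the change may not be free. The instrument is not shown, a score built partly from age, pressure or vasopressor use would add less, and intended collection in everyone does not guarantee complete data. In a complete-case model, about 4% missing scores would cancel a 4% gain (1 − 1/1.04 = 3.8%). This also stands. It calls for a missing-score rule and an honest range, but it does not remove the gain: overlap shrinks it without biasing the treatment contrast.

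A third reply is that the gain would seldom change a conclusion. Over most of the range that is fair, since the half-width narrows by 1.2 points at most.

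**Conclusion.** The point holds as a modest, avoidable loss of precision in the two mortality analyses. Under assumed mortality near 50% and severity effects of 0.3 to 1.1 log-odds per SD, adding severity is worth about 1% to 24% in effective sample size (260 × 0.009 = 2 to 260 × 0.235 = 61 patients), or 0.1 to 1.2 points off a half-width of about 11 to 12 points. Where in that range the trial falls cannot be settled from the article. The modified intention-to-treat set may also be smaller than 260, which widens both intervals.

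A reader might infer more than this, and the article does not support it:

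- **That the mortality estimate is biased, or that severity imbalance passes into it in full.** The estimate is unbiased over randomisation, and the listed covariates may absorb part of any imbalance.
- **That adding severity would materially raise power.** Gains of about 1 to 7 percentage points in power arise only if mortality truly differs by 15 to 17 points. The article states no mortality effect; its 15 points belong to the primary composite. For a 10-point reduction, unadjusted power is about 37% to 46%, and mortality stays underpowered with or without severity.
- **That mortality is the only outcome not itself defined by clinical decisions.** Hypotension is defined by a measured MAP below 65 mmHg.

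**What to change.** In the Statistical analysis section, name the baseline severity measure already collected as an additional covariate (a linear term if it is a score) in the models for ICU and in-hospital mortality, beside age, baseline MAP and vasopressor dose. In the same sentence:

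- state which instrument is meant, and that its values date from before randomisation;
- say whether site is in these models;
- give a simple rule for missing baseline scores, for example single or mean imputation of the covariate, so that no patient leaves the analysis.

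Leave the primary model as it is. If the investigators prefer not to adjust for severity, one line giving the reason would do.

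The cost is one extra covariate and a sentence or two of text. No new data are needed. The downside is small: a smaller gain if the score overlaps with age, MAP or vasopressor dose. The change should be recorded before the analysis starts.
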